**Methods/Design:**

A randomised, controlled, non-inferiority trial will be carried out in a predominantly rural area of Ethiopia. A sample of 324 people with SMD (diagnoses of schizophrenia, schizoaffective disorder, bipolar disorder or major depressive disorder) with an ongoing need for mental health care will be recruited from 1) participants in a population-based cohort study and 2) people attending a psychiatric nurse-led out-patient clinic. The intervention is a task-sharing model of locally delivered mental health care for people with SMD integrated into PHC delivered over 18 months. Participants in the active control arm will receive the established and effective model of specialist mental health care delivered by psychiatric nurses at an out-patient clinic within a centrally located general hospital. The hypothesis is that people with SMD who receive mental health care integrated into PHC will have a non-inferior clinical outcome, defined as a mean symptom score on the Brief Psychiatric Rating Scale, expanded version, of no more than six points higher, compared to participants who receive the psychiatric nurse-led service, after 12 months. The primary outcome is change in symptom severity. Secondary outcomes are functional status, relapse, service use costs, service satisfaction, drop-out and medication adherence, nutritional status, physical health care, quality of care, medication side effects, stigma, adverse events and cost-effectiveness. Sustainability and cost-effectiveness will be further evaluated at 18 months. Randomisation will be stratified by health centre catchment area using random permuted blocks. The outcome assessors and investigators will be masked to allocation status.

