### Sample size calculation

The following formula was used to calculate the required sample size (n):$$ n={2}^{*}{\left[\sigma /\Delta \right]}^2\;{\left({Z}_{\alpha }+{Z}_{\beta}\right)}^2, $$

where delta = non-inferiority margin (mean BPRS-E scores of six points), sigma is the standard deviation of the BPRS-E score (estimated standard deviation of 15 [57]), Z_alpha_ is the standardised mean difference for the probability of type 1 error (alpha = 0.05) and Z_beta_ is the standardised mean difference for the probability of type 2 error (beta =0.1 (that is, power of 0.9). Therefore, a sample size of 107 persons per arm of the trial (that is, a total of 214) is required [58]. No published studies from Ethiopia are available to guide us in our estimation of the intra-cluster correlation (ICC) for study subjects receiving treatment from a specific health centre. We therefore estimate the ICC to be 0.01, which is the median ICC from a review of 31 cluster-based interventions in PHC [59]. Given that there are 13 health centres within the three districts covered by the Ethiopia TaSCS trial, the design effect will be 1 + (n-1)*ICC (where n = number of subjects per cluster). Therefore, the design effect = 1 + (17–1)*0.01 = 1.16. Assuming a worst-case scenario of 30 % loss to follow-up, the required sample size = 214 * 1.30 * 1.16 = 323 participants. For equal numbers in each arm of the trial, the total sample size will be 324 (n = 162 in each arm).

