#### Data analysis approach

Data analysis will follow a detailed statistical analysis plan that specifies all planned analyses. Data analysis will take place using Stata Version 13 (Stata Corporation, College Station, Texas, USA) under the direction of the trial statisticians. All analyses will be masked to study arm until the analysis is finalized and approved by all investigators. Descriptive analyses will include frequency distributions and measures of central tendency and dispersion, as appropriate, with 95 % confidence intervals. Bivariable comparisons will employ χ^2^, Fisher’s exact, Student’s t- or rank-sum tests, as appropriate. All statistical tests will be one-sided at α = 0.05, as we are testing a hypothesis of non-inferiority and not superiority or equivalence.

Analysis will be by intention-to-treat, that is, on the basis of the group to which the participant is allocated randomly at the beginning of the trial. Intention-to-treat has the potential to lead to false acceptance of the hypothesis of non-inferiority in the presence of a true difference if there is a large cross-over from the primary care to the psychiatric nurse service [60]. Therefore, the intention-to-treat analysis will be presented together with the percentage of participants who deviate from the protocol in the following ways: (1) cross-over protocol deviation which is indicated by the percentage who attend for more than two consecutive visits at the service they were not randomised to receive, unless they were referred to that service, and (2) disengagement from care protocol deviation, which is the percentage who miss more than 50 % of their scheduled health facility appointments (not attending within 2 weeks of the appointment date). Per protocol analyses will also be conducted, and the findings presented as a sensitivity analysis. Account will be taken of clustering at the level of the health facility.

Analysis will be carried out on the complete data set at 12 and 18 months. For the primary outcome time-point of 12 months, it would not be appropriate to carry forward the last observation to replace missing data as this would have taken place at the baseline of the study and could, therefore, increase the chance of non-inferiority even in the presence of a difference between the allocated services.

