#### Analysis of primary outcome

The analysis for the primary outcome will be carried out by AHRI in order to ensure masking of the treatment group. The primary outcome measure (change in BPRS-E score) will be analysed using linear regression adjusting for baseline symptom severity. Statistical tests will be one-sided, reflecting our interest in testing the hypothesis that task-shared care is non-inferior. The validity of regression assumptions will be checked using residual plots. For the purpose of safety monitoring, the Phase 1 primary outcome at 12 months will be analysed as an interim analysis. For the purpose of hypothesis-testing for the main trial, Phase 1 and Phase 2 primary outcomes at 12 months will be combined. Both crude and adjusted (for baseline symptom severity, age and sex) effect sizes will be presented for the primary analysis. Exploratory analysis of the non-inferiority of the new intervention in the Phase 1 and Phase 2 participants will be carried out separately.

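### Clustering is set at the level of the health facility, but the control arm is one facility; facility-clustered standard errors would put false non-inferiority at about 11-13% instead of 5%

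*Protocol article*

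**What the plan says.** The control service is delivered by "psychiatric nurses at an out-patient clinic within a centrally located general hospital" (Abstract, Methods/Design). The section on the hospital out-patient clinic adds that no other mental health care exists in the trial districts. Task-sharing patients are treated at their local health centre. The sample size section counts 13 centres, and the eligibility criteria exclude one catchment, so 12 or 13 take part.

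Patients are randomised individually, stratified by health centre catchment area.

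On the analysis, Data analysis approach says "Account will be taken of clustering at the level of the health facility" and "All statistical tests will be one-sided at α = 0.05". Analysis of primary outcome says that the change in BPRS-E score "will be analysed using linear regression adjusting for baseline symptom severity". It names no method for clustering. Data analysis approach refers to a detailed statistical analysis plan, which is not shown.

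**The concern.** By treating facility, there are 12 or 13 clusters in one arm and one in the other. Routine methods for clustered data estimate uncertainty from variation between clusters, and a single cluster shows none. A method that relies on clusters within each arm therefore cannot see the control arm's error. A method that carries the between-centre variance over to the hospital charges that arm with a variance that one clinic cannot inform.

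The trial's conclusion rests on one one-sided confidence limit against 6 points. A standard error that is too small makes a false claim of non-inferiority more likely. One that is too large costs power. Data analysis approach already guards against false non-inferiority from cross-over and from carrying baseline values forward. This sentence opens another route to it.

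**Working it through.** **Inputs.** Margin 6 points, SD ("estimated standard deviation of 15"), ICC ("We therefore estimate the ICC to be 0.01"), one-sided alpha 0.05 and power ("that is, power of 0.9"), all from Sample size calculation; 162 per arm with 30% loss, so 162 × 0.70 = 113 analysed per arm; 12 or 13 centres.

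**The plan's own figure.** n = 2 × (15/6)² × (1.645 + 1.282)² = 107.05 per arm, against the stated 107. Then 214 × 1.30 × 1.16 = 322.7, so 323, as stated. The design effect uses 17 per cluster (214/13 = 16.5), which spreads both arms over the 13 centres.

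**Facility-clustered standard errors.** In a regression with an intercept and an arm indicator, the control residuals sum to zero. The clustered variance uses the residual sum within each cluster, so the single control cluster contributes nothing. With 113 per arm and 12 centres, and an ICC of 0.01 splitting 225 into 2.25 between centres and 222.75 within:

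- Task-sharing variance: 222.75/113 + 2.25/12 = 1.97 + 0.19 = 2.16.
- Control variance: 225/113 = 1.99.
- True standard error: √(2.16 + 1.99) = 2.04.
- Reported standard error: about √2.16 = 1.47.
- Ratio: √(2.16/4.15) = 0.72.
- False non-inferiority at a true difference of 6: P(Z > 1.645 × 0.72) = 11.8%.

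In simulation (6,000 runs per setting, Monte Carlo error about 0.4 percentage points) the mean reported standard error was 1.43 against a true 2.06, a ratio of about 0.70. Adding a baseline covariate did not cure it (10.8%). Nor does the ICC cause it: at ICC 0 the error was 11.7% (t reference) to 13.4% (normal reference).

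**Facility random intercept.** This model also assigns the between-facility variance to the one hospital, where nothing averages it out. Even with the variance known to be 2.25, the standard error would be √(1.97 + 0.19 + 1.97 + 2.25) = 2.53. In practice the variance is estimated from few small centres and cannot go below zero, so it is overestimated on average. The mean standard error was 2.90 against a true 2.03.

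**Results at ICC 0.01, no clinic effect in the control arm:**

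| Analysis | False non-inferiority at true difference 6 | Power at true difference 0 |
|---|---|---|
| Facility-clustered SE, t reference | 10.7-12.1% | not relevant |
| Facility-clustered SE, normal reference | 12.5-13.8% | not relevant |
| Facility random intercept | about 3% | 69% (113 per arm), 78% (162 per arm) |
| Clustering in the task-sharing arm only | 4.8-5.9% | 91% |
| SE clustered on catchment area, both arms | 4.6-5.8% | not computed |
| Linear regression, no clustering | 5.2-6.3% | not computed |

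The error ranges, apart from the random intercept, cover 8 to 13 centres, equal and unequal sizes, and 113 to 162 per arm. The 91% comes from a separate simulation with 13 centres of 9 patients and 114 controls.

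**The case against.** The strongest reply is that the sentence names no method. Modelling centre effects in the task-sharing arm only is one way of obeying it, and the choice of standard error and degrees of freedom is ordinary content for the analysis plan. The section on the primary outcome does not mention clustering, and without any adjustment the error is about 5-6%. This stands as a limit on the claim. A reader might infer that the trial will run at an 11-13% error rate, and the documents do not support that.

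Second, facility could be meant as the health centre catchment area. Randomisation is stratified by it, and the sample size section counts clusters as health centres with both arms spread over them. On that reading each cluster holds both arms and the error is near 5%. The reading is possible but not the natural one: the same paragraph in Data analysis approach uses facility for the appointments that define disengagement from either service, and the randomisation sections use the term catchment area when they mean residence.

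Third, the random intercept is too wide only if inference is about this clinic. If the clinic stands for nurse-led clinics in general and has its own effect at ICC 0.01, the random intercept's error is 5.1%, modelling the task-sharing arm alone gives 8.7%, and facility-clustered standard errors give 15-17%. That is a fair point about the target of inference. One clinic gives no data to estimate such an effect, so the target has to be declared.

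What survives is that the protocol does fix a level, and the literal use of that level in either routine method gives a wrong standard error for inference about this clinic.

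**Conclusion.** The point holds in conditional form. The treating facility is a badly chosen clustering level for a design in which one arm is a single facility, and the protocol does not acknowledge the imbalance. With facility-clustered standard errors on the planned regression, the standard error is about 30% too small and the one-sided error is about 11-13% against a nominal 5%. With a common facility random intercept, power is about 70% at 113 per arm against a planned 90%.

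These figures assume SD 15, ICC 0.01, about 113 to 162 analysed per arm, 8 to 13 centres and inference conditional on the one control clinic. At ICC 0.05 the facility-clustered error is still 9.6-11.1%. It would be wrong to conclude that every adjustment for clustering inflates the error, or that only one model is sound: two alternatives hold it near 5%, and the analysis plan may already use one of them.

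**What to change.** Replace the sentence in Data analysis approach with one of two rules, and state that it applies to the primary analysis:

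- Model clustering by allocated health centre in the task-sharing arm only, treat control patients as independent, and use small-sample degrees of freedom. Separate residual variances by arm and Satterthwaite degrees of freedom are one reasonable form, not the only one.
- Or cluster both arms on health centre catchment area, the randomisation stratum.

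In the first rule use the allocated centre, not the one attended, in keeping with the intention-to-treat analysis. Add that inference is conditional on the single control clinic. If the analysis plan already says this, the protocol sentence need only be aligned with it.

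The cost is a sentence or two and a few lines of code before unmasking, with no new data or patients. The interval will be wider than facility-clustered regression would report, and some degrees of freedom are lost.

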#### Interim analysis

An interim analysis will be conducted at 12 months. The DSMB will assess the primary outcome (BPRS-E score) and adverse events by arm of the trial and decide if there is evidence of inferiority of one arm, guided by the definition of clinical inferiority used for the primary hypothesis.

#### Analysis of primary outcome

The analysis for the primary outcome will be carried out by AHRI in order to ensure masking of the treatment group. The primary outcome measure (change in BPRS-E score) will be analysed using linear regression adjusting for baseline symptom severity. Statistical tests will be one-sided, reflecting our interest in testing the hypothesis that task-shared care is non-inferior. The validity of regression assumptions will be checked using residual plots. For the purpose of safety monitoring, the Phase 1 primary outcome at 12 months will be analysed as an interim analysis. For the purpose of hypothesis-testing for the main trial, Phase 1 and Phase 2 primary outcomes at 12 months will be combined. Both crude and adjusted (for baseline symptom severity, age and sex) effect sizes will be presented for the primary analysis. Exploratory analysis of the non-inferiority of the new intervention in the Phase 1 and Phase 2 participants will be carried out separately.

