#### Butajira hospital psychiatric out-patient clinic

In Butajira, the general hospital has a psychiatric out-patient clinic run by psychiatric nurses. At present this clinic is the only mental health care available within the districts covered by the TaSCS trial, as is the case in most of Ethiopia [37]. Since completion of the Butajira SMD cohort recruitment, additional people with SMD living in the Butajira SMD/TaSCS recruitment area have sought care from this clinic because they are (1) incident cases, (2) missed cases from the original recruitment, or (3) they have migrated into the area. If the TaSCS trial is unable to recruit a sufficient sample size from the Butajira SMD cohort, consecutive attendees at the Butajira hospital psychiatric clinic will be screened for eligibility.

Recruitment into the trial will be divided into two phases. In Phase 1, only people with SMD who are clinically stable will be recruited. Three months after beginning recruitment, the Data Safety and Monitoring Board (DSMB) will review adverse events, including non-engagement with the service, disengagement from care and evidence of potentially dangerous prescribing, before Phase 2 recruitment is permitted. In Phase 2, people with SMD who have more complex needs or who are clinically unstable will be recruited.

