### Randomisation and service allocation

#### Sequence generation and allocation concealment

A computerized system will be used to generate a randomization list. The randomization will be stratified by health centre catchment area. Within each health centre catchment area, randomization will be organized with permuted blocks of random size so that an equal number will be randomized to the new intervention arm and to the active control arm. From the randomization list, labelled and sealed envelopes will be prepared containing cards with intervention allocation. The sealed envelopes will be handed over to independent clinicians working in Butajira hospital and will be kept in a secure place.

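### The primary model leaves out the randomisation stratum, and the plan does not say which of three estimates is compared with the 6-point margin

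*Protocol article*

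**What the plan says.** Allocation (Protocol article, Sequence generation and allocation concealment): "The randomization will be stratified by health centre catchment area". The same section continues: "Within each health centre catchment area, randomization will be organized with permuted blocks of random size".

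Primary analysis (Analysis of primary outcome): change in BPRS-E "will be analysed using linear regression adjusting for baseline symptom severity". Later in the same paragraph: "Both crude and adjusted (for baseline symptom severity, age and sex) effect sizes will be presented for the primary analysis". On the two recruitment phases, it says "Phase 1 and Phase 2 primary outcomes at 12 months will be combined" for the hypothesis test, and "Exploratory analysis of the non-inferiority of the new intervention in the Phase 1 and Phase 2 participants will be carried out separately".

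Clustering (Data analysis approach): "Account will be taken of clustering at the level of the health facility". Tests are one-sided at 0.05.

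The Hypothesis and Primary outcome sections define non-inferiority on the mean BPRS-E score, with a margin of six points; the analysis section speaks of change in score.

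**The concern.** There are two linked gaps.

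- **The stratum is absent from the model.** Blocking within catchment area removes between-catchment variation from the arm comparison. A model without catchment area leaves that variation in the residual, so its standard error does not match the design. A facility term does not repair this. In the intervention arm, facility broadly corresponds to catchment. In the control arm there is a single facility, the Butajira hospital clinic, whatever the patient's catchment.
- **No estimate is named as decisive.** Three specifications appear: baseline only; crude; and baseline with age and sex. The last two share the label of primary analysis. Nothing says which upper bound is set against 6. If crude and adjusted bounds fall on opposite sides of the margin, the trial has no defined answer, and a choice made after seeing them would raise the chance of a false claim.

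**Working it through.** **Inputs from the protocol (Sample size calculation):** margin 6, SD 15, one-sided alpha 0.05, power 0.90, ICC 0.01, 30% loss, 324 randomised.

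**Assumptions (not in the protocol):** correlation r between baseline and 12-month BPRS-E of 0.3, 0.5 or 0.7; the same SD of 15 at both times; normal approximation.

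**1. The plan's own figure.** n per arm = 2 × (15/6)² × (1.645 + 1.282)² = 107.05, against the stated 107. Inflation as written: 214 × 1.30 × 1.16 = 322.7, against the stated 323. Both reproduce. After 30% loss, 324 × 0.70 = 226.8, so about 113 per arm are analysed.

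**2. Omitting the stratum.** If catchment explains a share of variance equal to the ICC, the correct standard error is √(1 − ICC) times the one ignoring it. Power is Φ(6 / (15 × √(1 − ICC) × √(2/113)) − 1.645).

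| ICC | SE factor | Power |
|---|---|---|
| stratum ignored | 1 | 0.913 |
| 0.01 (plan) | 0.995 | 0.916 |
| 0.05 (assumed) | 0.975 | 0.925 |

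The plan's ICC is for patients treated at the same health centre; using it as the catchment share is an approximation. The direction is clear: the interval is slightly too wide, and the contrast is not biased.

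**3. Crude against baseline-adjusted.** With baseline in the model, the arm coefficient is the same for change and for the 12-month score, so that difference of wording affects only the crude estimate. Taking crude as the change score the analysis section names:

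- adjusted SE = 15 × √(1 − r²) × √(2/113)
- crude SE = 15 × √(2(1 − r)) × √(2/113)
- ratio of the SEs, which is also the correlation of the two estimates = √((1 + r)/2)

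Each analysis declares non-inferiority with probability Φ((6 − d)/SE − 1.645) at true difference d. The bivariate normal gives the probability that both do, and so the probability that exactly one does (disagreement) and that at least one does.

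| r | Adjusted SE | Crude SE | Ratio | Disagree, d = 0 | Disagree, d = 3 | At least one claims, d = 6 |
|---|---|---|---|---|---|---|
| 0.3 | 1.90 | 2.36 | 0.81 | 14.0% | 21.8% | 7.5% |
| 0.5 | 1.73 | 2.00 | 0.87 | 6.4% | 18.2% | 7.1% |
| 0.7 | 1.42 | 1.55 | 0.92 | 0.9% | 12.7% | 6.6% |

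A simulation (226 analysed, 13 strata, blocked 1:1, 2000 runs per setting) gave disagreement of about 16%, 6% and 1% at d = 0 and 21%, 18% and 12% at d = 3, in line with the table.

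**4. If crude means the 12-month score** (as in the Hypothesis section), the crude SE is 2.00 throughout and the correlation of the estimates is √(1 − r²). For r = 0.3, 0.5 and 0.7, disagreement is then 3.8%, 6.4% and 8.3% at d = 0, and 9.9%, 18.2% and 30.9% at d = 3. The chance that at least one claims at d = 6 is 6.2%, 7.1% and 8.0%. The trend with r reverses, but the conclusion does not.

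**5. The two adjusted specifications.** In the same simulation, where age and sex did not lower the standard error, baseline-only and baseline-age-sex verdicts disagreed in at most about 3% of trials. The choice that matters is crude against adjusted.

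**The case against.** The strongest reply is that a model is named. The baseline-adjusted regression comes first in the section, and the later sentence on crude and adjusted effect sizes concerns what will be presented. No sentence allows either result to carry the claim. The protocol also refers to a detailed statistical analysis plan, not shown here, where a decisive estimate and stratum terms are commonly fixed. This has force: the 6.6 to 7.5% is what an either-result rule would produce, not the plan's stated error rate. But the article chose to state the models, gave two different adjusted covariate sets, and attached the primary label to a crude estimate as well. That inconsistency is in the text.

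It is also fair that the stratum's effect is negligible at the plan's ICC and errs on the safe side.

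Three stronger readings are tempting and not supported.

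- **That pooling the phases without a phase term is a material flaw.** The protocol says "In Phase 2, people with SMD who have more complex needs or who are clinically unstable will be recruited", which suggests a difference in prognosis, but it gives no figure for one. Baseline BPRS-E already captures part of any difference, and several of the extra Phase 1 criteria (breast-feeding, depot prescription, medical co-morbidity) are not symptom severity. Sequential blocks within catchment keep the arms roughly balanced across phases, so no bias follows. Where the simulation carried a 6-point phase difference through baseline, adding stratum and phase together changed the mean SE by 0.6% or less.
- **That the separate phase analyses are underpowered tests.** With 124 × 0.7 / 2 = 43.4 and 200 × 0.7 / 2 = 70 per arm, power is about 59% and 76%. At least one would fail in 1 − 0.586 × 0.765 = 55% of trials with equal arms. The protocol labels them exploratory, however, and no conclusion requires both to pass.
- **That omitting the stratum raises false non-inferiority.** It does the opposite, slightly.

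**Conclusion.** The point holds in two parts. First, catchment area is a stratification factor that no listed primary model contains, and facility clustering does not replace it. The cost is small and conservative: about 0.5% of the standard error at ICC 0.01, about 2.5% at an assumed 0.05. The reason to include it is mainly that the analysis should follow the design. Second, and of more consequence, three specifications sit under one decision with no statement of which bound is compared with 6. With crude as the change score and correlations of 0.3 to 0.7, discordant verdicts arise in about 1 to 14% of trials with equal arms and about 13 to 22% at a true difference of 3 points. The false-claim rate would be about 6.6 to 7.5% only if either result were allowed to decide, which the protocol does not say. These figures rest on the assumed correlations and on the plan's SD and loss to follow-up. The unseen analysis plan may already settle the matter.

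**What to change.** Before unmasking, state one decisive model: 12-month BPRS-E (or change) on arm, baseline BPRS-E, catchment area, age and sex, with the promised allowance for facility clustering. Compare its one-sided 95% upper bound with 6. Label the crude and any other adjusted estimates as supportive, and say whether crude means the change score or the 12-month score.

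A phase term is optional. It costs one degree of freedom, and its gain is unknown and probably small once baseline is in the model. The phase-specific analyses can stay exploratory, reported as estimates with confidence intervals.

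The cost is one paragraph. Every variable is already collected and no patients are added. With up to 13 catchments, the model has 17 coefficients (intercept, arm, baseline, 12 for catchment, age, sex), which leaves 226 − 17 = 209 residual degrees of freedom.

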#### Butajira SMD cohort

The Butajira SMD population-based cohort was established between 1998 and 2001 [5]. People with possible SMD were identified in two ways: (1) through a house-to-house survey covering 68,378 people using the Composite International Diagnostic Interview (CIDI) [33] as a screening tool, and (2) through community key informants, who had been trained using vignettes describing typical presentations of SMD [34]. All potential cases were invited for a second phase clinician assessment conducted by an Ethiopian physician using the Schedule for Clinical Assessment in Neuropsychiatry (SCAN) [35]. Of the 2285 SCAN assessments conducted, 844 people were diagnosed as having SMD and recruited into the cohort. Incident cases (n = 75) from the geographical catchment area over the next 2 years also underwent confirmatory diagnosis with SCAN and were recruited into the cohort, giving a total of 919 people with SMD: 359 with schizophrenia or schizoaffective disorder, 345 with bipolar disorder and 215 with severe major depressive disorder [13]. After 10 years (2011/2012) of follow-up, a clinician assessment was carried out using the Longitudinal Interval Follow-up Evaluation (LIFE) chart [36]. At that time, loss to follow-up from the cohort was as follows: 121 had died, 112 had refused to continue study assessments, 15 were vagrant and 70 had changed address and were not contactable. Study participants were more likely to be lost to follow-up if they were male, unmarried, had a diagnosis of schizophrenia and were more severely unwell at baseline, although the differences were small. However, loss to follow-up was not associated with age, literacy or employment status. The Butajira SMD cohort is one of the very few population-based studies of SMD from a LMIC. Even with the potential attrition bias, the Butajira SMD cohort offers a unique opportunity to obtain a sample that is free from the substantial selection bias associated with facility-based recruitment and is potentially more generalisable to people with SMD, who would access task-shared mental health care in PHC.

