If more than 15 % of the primary outcome scores are missing, we will conduct multiple imputation analysis (including age, sex, baseline symptom severity and substance use disorder) in the model and present this as an exploratory analysis alongside the analysis on the complete dataset.

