#### Analysis of secondary outcomes

These analyses will be carried out by the trial statisticians. The planned approach for data analysis of secondary outcomes is outlined in Additional file 3. Multivariable analysis will be used to adjust for the following potential confounding variables measured at baseline: age, sex, socioeconomic status, substance use and symptom severity.

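### The imputation model omits diagnosis and marital status, which the protocol links to loss from the source cohort, and diagnosis is in no listed covariate set

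*Protocol article*

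**What the plan says.** All references are to the Protocol article.

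- **Butajira SMD cohort.** Members of the source cohort were "more likely to be lost to follow-up if they were male, unmarried, had a diagnosis of schizophrenia and were more severely unwell at baseline", and the sentence goes on "although the differences were small". The section adds that "loss to follow-up was not associated with age, literacy or employment status". The follow-up was about 10 years.
- **Data analysis approach.** The analysis is on complete data at 12 and 18 months. If more than 15% of primary outcome scores are missing, multiple imputation is added as an exploratory analysis, with its variables given as "including age, sex, baseline symptom severity and substance use disorder".
- **Analysis of primary outcome.** The main linear regression adjusts for baseline symptom severity. In addition, "Both crude and adjusted (for baseline symptom severity, age and sex) effect sizes will be presented for the primary analysis".
- **Analysis of secondary outcomes.** The covariates are "age, sex, socioeconomic status, substance use and symptom severity".
- **Potential confounders and Table 2.** Marital status is recorded at baseline among the sociodemographic variables. Adjustment is foreseen if variables turn out unequally distributed by chance. Diagnosis is not on the list.
- **Eligibility criteria.** Every participant has a DSM-IV diagnosis from a standardised assessment before entry.

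**The concern.** The protocol names four correlates of loss in the population from which it recruits, then names its covariates one by one, and two of the four do not appear. This is not a detail left open for the analysis plan, because the lists are given.

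The omission matters most in the imputation model. The sample size allows for 30% loss, twice the 15% that triggers imputation, and no other stated analysis deals with missing primary outcomes. If both loss and the 12-month score depend on diagnosis given the variables in the model, an imputation model without diagnosis leaves that bias in place. The same applies to the complete-data regression. Conversely, when loss depends only on variables in that regression and the treatment effect does not vary across them, the complete-data estimate is not biased by the loss. Having diagnosis in the adjusted primary model therefore protects the analysis on which the conclusion rests.

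In a non-inferiority trial, losing more of the patients with worse outcomes from the new service would favour the new service.

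**Working it through.** **1. Setting the lists side by side**

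| Correlate of cohort loss | Imputation | Main primary regression | Adjusted primary | Secondary | Listed confounders |
|---|---|---|---|---|---|
| Sex | yes | no | yes | yes | yes |
| Baseline severity | yes | yes | yes | yes | measured as the outcome |
| Marital status | no | no | no | no | yes |
| Schizophrenia diagnosis | no | no | no | no | no |

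Socioeconomic status in the secondary list does not cover marital status: Table 2 defines it by education, occupation, food insecurity and family size. The covariates of the economic model are not itemised, so it is left out.

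**2. The plan's own figures**

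Sample size: 2 × (15/6)² × (1.645 + 1.282)² = 107 per arm, 214 in total. Then 214 × 1.30 × 1.16 = 322.7, so 323, made even at 324. The stated figures reproduce, and adding covariates does not change them.

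Cohort loss: "121 had died, 112 had refused to continue study assessments, 15 were vagrant and 70 had changed address and were not contactable", so 121 + 112 + 15 + 70 = 318 of 919, or 34.6%. Schizophrenia or schizoaffective disorder: p = 359/919 = 0.391.

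**3. Size of the bias from leaving diagnosis out**

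From the documents: p = 0.391 (share of the original cohort, taken as a stand-in for the trial) and overall loss L = 0.30.

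Assumed, because the documents give no figures: the excess loss d in people with schizophrenia, in one arm only, and the gap g in 12-month BPRS-E between them and the others, given baseline.

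- Loss in the others = L − p·d; loss in schizophrenia = L − p·d + d.
- Fall in the schizophrenia share among completers of that arm = p(1 − p)d/(1 − L) = 0.391 × 0.609 × d/0.70 = 0.340·d.
- Bias in the arm difference = 0.340·d·g.

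| d | Loss, schizophrenia v others | Fall in share | g = 3 | g = 5 | g = 10 |
|---|---|---|---|---|---|
| 0.05 | 33.0% v 28.0% | 0.017 | 0.05 | 0.09 | 0.17 |
| 0.10 | 36.1% v 26.1% | 0.034 | 0.10 | 0.17 | 0.34 |
| 0.20 | 42.2% v 22.2% | 0.068 | 0.20 | 0.34 | 0.68 |

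The range is 0.05 to 0.68 points, or 0.8% to 11% of the 6-point margin. Opposite patterns in the two arms would double it. The same pattern in both arms, with an effect that does not vary by diagnosis, gives about zero.

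**4. What a small difference would do to the error rate**

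Take d = 0.05 and g = 8: bias = 0.017 × 8 = 0.14. With 324 × 0.70/2 = 113.4 completers per arm, SE = 15 × √(2/113.4) = 1.99, ignoring clustering and baseline adjustment. The one-sided error is Φ(0.136/1.99 − 1.645) = 5.7%, against a nominal 5%.

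**The case against.** The evidence on loss is indirect. It covers about 10 years, 121 of the 318 losses were deaths, and the trial takes people who are still reachable and plan to stay at least 18 months. The protocol calls the differences small. Outcome assessments are held away from the clinics and participants are compensated for transport and time, so leaving care is not the same as missing the BPRS-E. All of this stands, and it places the plausible bias towards the lower end of the table.

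The text is also somewhat open. The word that introduces the imputation variables need not mean a closed list, and marital status could be adjusted for if unbalanced. This helps only in part: the confounder provision deals with chance imbalance at baseline, not selective loss, and it does not list diagnosis.

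Three stronger readings are tempting, and the documents do not support them.

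- **That the false non-inferiority rate is seriously inflated.** That would need, for example, loss about twice as frequent in schizophrenia, confined to the primary care arm, together with a large BPRS-E gap. The protocol says a new treatment setting may be unsettling, but gives no figure for arm-specific loss. Excess loss in the control arm would bias against non-inferiority.
- **That adjusting for age is a mistake because age was unrelated to loss.** A covariate may serve prognosis or confounding and need not predict loss. Nor is age in every model: the main primary regression adjusts for baseline severity only.
- **That baseline BPRS-E carries no information on diagnosis because patients enter stable.** The stability criterion applies to Phase 1, 124 of 324 participants, and admits stable residual symptoms. The 200 in Phase 2 may be unstable.

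**Conclusion.** The point holds as a modest, nearly free improvement. Two of the four correlates of loss that the protocol itself reports are missing from the only model it offers for missing primary outcomes, and diagnosis is in no listed covariate set at all. The likely effect on the estimate is small: 0.05 to about 0.7 points against a margin of 6 over the assumed range, and near zero under a common pattern of loss in both arms with an effect that does not vary by diagnosis. The arm-specific excess loss and the BPRS-E gap are assumptions, and the 39% share is that of the original cohort. The documents do not show that diagnosis predicts the 12-month score given baseline, so a gain in precision is possible but not established. The concern does not put the trial's conclusion in doubt.

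**What to change.** - **Data analysis approach:** add diagnosis (schizophrenia or schizoaffective disorder, bipolar disorder, major depressive disorder) and marital status to the named imputation variables. Keep age, sex, baseline severity and substance use disorder.
- **Analysis of primary outcome:** add diagnosis in the same three groups to the pre-specified adjusted model. Keep baseline severity, age and sex.
- If the sponsor wants the outcomes handled alike, the secondary-outcome list can take diagnosis as well.

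The cost is a few degrees of freedom (two for diagnosis) and a wording change. Diagnosis is known from eligibility and marital status from the baseline interview, so no new data or participants are needed. The change should be fixed before unmasking, because diagnosis added afterwards could be challenged as post hoc.
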